## Data analysis

### Primary feasibility outcomes

The recruitment rate, completion rate, and compliance with the intervention (intervention days, content and duration of each physiotherapy session and tablet use) will be described using descriptive statistics. Descriptive data analysis included the determination of absolute and percentage frequencies, medians, means, minimum and maximum values, standard deviations, and 95% confidence intervals using the commercial software IBM SPSS Statistics 25.0.

To assess feasibility, the defined criteria for determining success (s. Table 1) will be used in combination with the feasibility assessment criteria from Thabane’s framework [48]. The feasibility milestones were defined pragmatically based on prior project experience, organisational capacities in the participating regions, and values considered acceptable in comparable feasibility contexts. They are intended to guide interpretation of feasibility rather than to function as rigid pass-fail criteria. The final decision regarding the overall feasibility rating of the study protocol will be based on pragmatic considerations of the feasibility of the protocol in terms of recruitment, data collection, and the impact on professionals’ workflows. In addition, the judgment of the research team will be taken into account, which will encompass an assessment of the capacity to influence individual barriers and problems, for example through counselling or training.

Acceptability and individual compliance with the intervention, assessed through interviews at the 20-week follow-up, will be analysed using content analysis, which comprises a combination of inductive and deductive procedures, according to Mayring [49]. The interviews will be audio recorded and transcribed verbatim for analysis. MAXQDA (VERBI software, Berlin, Germany) will be used for transcription and analysis. The primary focus of the qualitative data analysis will be on answering the central research questions. It will cover general experiences and user behaviour related to the new intervention, problems and areas for optimisation, changes in physical activity, and changes in interaction and social participation. The analysis will be conducted by two independent members of the research team.

Qualitative findings will also be used to explain and contextualise quantitative feasibility results, such as low adherence, incomplete data, or barriers and facilitators for implementation. Integration of qualitative and quantitative findings will take place at the interpretation stage through joint comparison of results across feasibility domains (e.g. recruitment, intervention uptake, acceptability, and adherence). This convergent mixed-methods approach will enable a more comprehensive assessment of feasibility than either data stand alone.

### Secondary outcomes

The secondary patient-related outcomes and additional measures also will be described using descriptive statistics. Exploratory analyses of potential benefit will focus primarily on within-group change over time and descriptive comparison of change patterns across groups. The main purpose of these within-group comparisons is to determine whether the selected assessments are suitable for capturing changes in outcomes over time and to assess the preliminary patterns of change of the novel intervention prior to testing it in a main trial. The data will also provide information to estimate variability.

Any inferential analyses will be interpreted cautiously and as hypothesis-generating only. Additionally, exploratory inferential statistical data analysis will be used, including mean comparisons, correlations, and regressions to identify and describe patterns. The chi-square (χ^2^) test will be used to compare categorical variables. An odds ratio with a 95% confidence interval will be calculated as an effect measure.

Given the small sample size, formal subgroup analyses are not planned. At most, descriptive exploration of selected participant characteristics may be undertaken if this appears useful for interpreting feasibility outcomes. Missing data will be reported descriptively.

Given the nature of the intervention, we do not expect serious adverse events. Thus, no interim analysis is planned, and no stopping rules will be applied as regards safety issues. There is also no necessity for a data monitoring committee.

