### 3rd phase - pilot study and evaluation

During piloting of the intervention, data for outcomes and other variables will be collected continuously (e.g. recruitment rates, content and duration of physiotherapy and tablet use) or at three measurement points: at baseline (T0), after 12 weeks (T1, end of physiotherapy treatment), and after 20 weeks (T2, follow-up). An overview of the different primary and secondary outcome variables is provided in Tables 1 and 2.

**Table 1 Tab1:** Primary feasibility outcomes

Outcome	Definition/measurement	Data source	Success threshold
Recruitment rate patients	Proportion of patients approached who meet the eligibility criteria and agree to enter the study; Reasons for agreement or disagreement	Recruitment protocol general practitioner; interview with patients and general practitioner at T2^c^	> 50%
Recruitment rate professionals	Proportion of physiotherapist and general practitioners approached who agree to enter the study; Reasons for agreement or disagreement	Recruitment protocol study team; interview with physiotherapists and general practitioner at T2^c^	> 30%
Completion rate	Proportion of all study patients that remain participants until the end of the defined study period	Study management protocol	≥ 95%
Compliance with the intervention	Proportion of all patients who receive a scheduled, individually digital exercise plan	Documentation physiotherapist	100%
	Proportion of all patients who used the tablet for exercise at least one day per week; content and duration of each tablet usage	Tablet user data	≥ 80%
	Proportion of all patients who used the tablet for gaming at least one day per week; content and duration of each tablet usage	Tablet user data	≥ 80%
	Proportion of perceived video calls that were suggested by the PT; content and duration of each physiotherapy session	Documentation physiotherapist	≥ 80%
Compliance with study procedures	Proportion of complete data	Study management protocol	≥ 90%
	Proportion of participants who rate assessments as feasible to use	Interview with patients, physiotherapists and general practitioners at T2^c^	≥ 80%
	Proportion of participating professionals who rate the study procedures as feasible		≥ 80%
	Proportion of participants who use the supporting materials provided by the study team		≥ 80%

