Acceptability	Views and experience of the intervention, amount of perceived barriers and facilitators	Interview with patients, physiotherapists and general practitioners at T2^c^	Not applicable
	Attitude and experience with modern technology	Patient questionnaire at T0^a^, T1^b^ and interview at T2^c^	

^a^*T0*: baseline assessment

^b^*T1*: 12-week follow-up (end of physiotherapy)

^c^*T2*: 20-week follow-up

**Table 2 Tab2:** Secondary patient-related outcomes

Outcome	Instrument	Data source	Measurement point
Balance, walking speed, strength of the lower extremities	Short Physical Performance Battery, SPPB [42]	Physiotherapist	T0^a^, T1^b^
Physical activity in everyday life and sporting activities, including facilitators and barriers to physical activity adherence, and the intention to carry out regular physical activity (at least 30 min on at least 5 days a week)	Freiburg Physical Activity Questionnaire, FFB [46] and additional items	Patient-reported via questionnaire (T0, T1) or interview (T2)	T0, T1, T2^c^
Activities of daily living	Hannover Functional Ability Questionnaire (FFbH) [47]		T0, T1
Quality of life and well-being	Short-Form Health Survey, SF-8 [43]		T0, T1
Social situation and social contacts	Social Situation (Part 1), SoS [45]		T0, T1
Falls and fall-related treatment	Fall assessment, self-generated items		T0, T1

^a^*T0*: baseline assessment

^b^*T1*: 12-week follow-up (end of physiotherapy)

^c^*T2*: 20-week follow-up

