## Ethical and legal considerations

The research team will be responsible for ensuring that research participants have the opportunity to address any sense of burden and maintain their well-being. Any changes to the study protocol, expected or unexpected serious events, or early termination of the study will be promptly reported to the ethics committees by the principal investigators.

Participating patients are covered by insurance, as there is a risk of an unintentional fall due to independent exercise at home. However, the selected exercises will be according to the physiotherapeutic assessment and the patients’ resources, which help to minimise the risk of falling. Before the patients carry out the selected exercises independently at home, they will practice them face-to-face under therapeutic supervision during an appointment. Patients also will receive information on safety measures.

All participants will be informed that study-related data will be stored in pseudonymised form and will only be used for scientific data analysis. The study data will be kept in a locked archive for 10 years at the study centre after completion of the trial and will then be deleted. Additionally, the EU General Data Protection Regulation will apply, and all participants will be explicitly informed about their rights.

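### Falls, the one intervention harm the protocol names, are scheduled only at T0 and T1, so the falls outcome omits weeks 12 to 20 and patients who leave before T1

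*Protocol article*

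**What the plan says.** **Safety rationale.** The Secondary outcomes part of the Data analysis section states: "Given the nature of the intervention, we do not expect serious adverse events". It continues: "Thus, no interim analysis is planned, and no stopping rules will be applied as regards safety issues", and adds: "There is also no necessity for a data monitoring committee".

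**Recognised risk.** Under Ethical and legal considerations: "Participating patients are covered by insurance, as there is a risk of an unintentional fall due to independent exercise at home". The same paragraph lists measures that reduce the risk: selection of exercises after a physiotherapeutic assessment, supervised practice beforehand, and safety information.

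**Falls outcome.** The last row of Table 2 covers falls and their treatment. The instrument is "Fall assessment, self-generated items" and the measurement points are T0 and T1. The patient-reported rows share a data-source cell that assigns questionnaires to T0 and T1 and an interview to T2. Of these rows, only physical activity is also listed at T2.

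**Other routes for harms.** The outcome section has physiotherapists record problems at every face-to-face or online session. Under Ethical and legal considerations, "expected or unexpected serious events, or early termination of the study will be promptly reported to the ethics committees". The Quality assurance section promises a plan concerned with safety, with SOPs for research staff, general practitioners and physiotherapists.

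**The concern.** A feasibility study of unsupervised home exercise in people aged 65 or older with impending or existing functional limitations should tell the planners of the main trial how often participants fall. The schedule limits this in two ways.

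First, the T2 contact already exists and is used to ask about physical activity, but falls are not listed there. The interview topics given in the outcome and analysis sections do not name them either. Activity is followed to week 20 and falls stop at week 12, although the study is interested in long-term adherence and names fall prevention among its aims.

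Second, a patient who leaves before week 12 fills in no T1 questionnaire, and the article describes no falls question at withdrawal. If a fall is the reason for leaving, that fall is missing from the outcome. The loss is then related to the event being counted, and the count is biased downwards.

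A third, smaller matter is wording. The paragraph that justifies the safety arrangements appeals to the nature of the intervention and does not mention the one hazard of that intervention which the ethics section names.

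**Working it through.** The plan states no fall rate or safety figure, so there is none to reproduce. The check is a comparison of the schedule with follow-up, plus arithmetic for scale.

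**1. Time covered by the falls outcome.** T1 is at week 12 and T2 at week 20 (section on the 3rd phase). The recall period of the falls items is not given; I assume that T1 asks about the time since T0.
- Weeks not covered: 20 − 12 = 8; 8/20 = 40% of follow-up.
- Prescribed home exercise lasts 12 weeks (Intervention group section). For patients who complete T1, the exercise period is covered and the gap lies after it.
- Person-time for 30 intervention patients: 30 × 20/52 = 11.5 person-years to T2, of which 30 × 8/52 = 4.6 fall after T1.

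**2. Falls expected in the gap.** The rates below are my assumptions.
- At 0.3 to 0.6 falls per person-year, all 20 weeks: 11.54 × 0.3 = 3.5 to 11.54 × 0.6 = 6.9 falls.
- Weeks 12 to 20: 4.62 × 0.3 = 1.4 to 4.62 × 0.6 = 2.8 falls.
- Counting people instead, with 20% to 50% falling at least once a year and a constant hazard, the risk over 8 weeks is 1 − (1 − p)^(8/52). This gives 0.034 to 0.101, or 1.0 to 3.0 fallers among 30. The chance of at least one is 1 − (1 − p)^(30 × 8/52), that is 0.64 to 0.96.

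**3. Patients who leave before T1.** Table 1 sets completion at 95% or more.
- 29/30 = 96.7% meets this and 28/30 = 93.3% does not, so at most 1 of 30 may leave. For both groups, 57/60 = 95%, so at most 3 of 60.
- With the same 20% to 50% assumption, 30 × [1 − (1 − p)^(12/52)] gives 1.5 to 4.4 expected fallers in weeks 0 to 12. If the one permitted loss were a faller, that would be 1/4.4 = 23% to 1/1.5 = 67% of the expected number. This illustrates the leverage of one patient at this sample size. It does not estimate the bias, which cannot be sized from the document.

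**4. Do the other routes fill the gap?**
- Session notes record problems met in sessions, but the named hazard arises in exercise between sessions. Controls have one session a week, while intervention patients agree their session frequency individually, so the notes may also differ in intensity between groups.
- Serious-event reporting covers serious events only, and many falls will not be serious.
- The quality assurance plan, as described, does not mention falls.

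These routes can bring individual falls to light. None asks every patient the same question over a defined period.

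**The case against.** Several stronger readings are tempting, and the document does not support them.

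- **That the two sections contradict each other, or that harm is dismissed.** One speaks of serious adverse events, the other of falls. Most falls need not be serious, so insuring against falls while not expecting serious events is consistent. The plan also lists measures to reduce risk and commits to reporting serious events. What stands is that the rationale omits the named risk.
- **That falls go unnoticed by the study team until a week-12 form arrives.** Session documentation and serious-event reporting are stated. How events reach the team is detail that an article may leave to the full protocol and the SOPs, so its absence here is no finding.
- **That 40% of the exercise exposure is unobserved.** The 8 weeks follow the prescribed exercise. In completers, T1 covers the treatment period, so the gap concerns follow-up. Falls might also be volunteered in the T2 interview.
- **That zero events in 30 shows the weakness of the capture.** The exact two-sided upper limit, 1 − 0.025^(1/30) = 11.6%, comes from the sample size and would be the same with perfect capture.
- **That safety must be a Table 1 criterion.** That is a preference. Falls are already a secondary outcome.

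A fair practical objection also stands. Control data collection had begun, and the Design section intends the measurements to stay the same apart from tablet use. New fall questions at each session would apply mainly to the intervention group and would raise its count through closer questioning alone. For that reason the fix adds no session-level items.

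**Conclusion.** The point holds as a gap in a stated schedule. Table 2 fixes falls at T0 and T1 only, while the same table uses T2 for physical activity. The falls outcome therefore leaves out 8 of 20 weeks and all patients lost before T1, and it is biased low to the extent that falls cause withdrawal.

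The size is modest: about 1.4 to 2.8 falls (1.0 to 3.0 fallers) in the omitted weeks among 30 intervention patients, under assumed rates that the document does not supply. The withdrawal effect is limited to one patient in 30 if the completion target is met and is larger if it is not. Its direction is clear under fall-related withdrawal, but its size is unknown.

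A reader might go on to infer that the safety arrangements are unsound or that the study has no way of learning of serious falls. The text does not support either. This is a cheap improvement to the falls outcome and to one sentence of rationale.

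**What to change.** 1. Add T2 to the falls row of Table 2, using the existing interview and asking about the time since the last completed falls questionnaire.
2. Ask the same falls items when a patient leaves early.
3. Report falls descriptively per person-time for all enrolled patients, with their observed time as denominator, and note whether each fall occurred during study exercise.
4. Reword the safety rationale in the Secondary outcomes part of the analysis section so that it acknowledges the fall risk named under Ethical and legal considerations.
5. Limit any comparison between groups to the T0 and T1 questionnaire common to both, and show falls collected by the new routes separately. Control data collection had begun, and the full interviews are described for the intervention group, so control data from T2 and withdrawal may be incomplete.

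**Cost.** One item in the interview guide, the same items at withdrawal, and a protocol change to be reported to the ethics committees. No extra visit is needed. The Trial status section places the start of intervention recruitment after submission, so the change could apply from the first intervention patient. If recruitment has since started, it can be made only for patients still in follow-up, and the report should say from when it applied.

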## Quality assurance

The study will be planned, implemented and evaluated in accordance with the principles of good clinical practice [50] and the Declaration of Helsinki [51]. Following ethical approval, the study was registered with the publicly accessible German Clinical Trials Register (DRKS) under the ID DRKS00031574 before any study participants were enrolled. This study protocol will be published in a peer-reviewed journal and it will follow the most recent Standard Protocol Items: Recommendations for Interventional Trials (SPIRIT) statement [52] and the applicable criteria from the extension of the Consolidated Standards of Reporting Trials (CONSORT) for randomised pilot and feasibility trials [36]. The corresponding checklists are presented in Additional files 1 and 2.

A detailed quality assurance plan will be developed to ensure safety. This plan will summarise the monitoring methods for data collection, validation and reporting, and will include SOPs to provide research staff, general practitioners and physiotherapists with instructions for data collection, handling, reporting and analysis.

To ensure wide dissemination, we will publish the study results in peer-reviewed scientific journals and present the results at scientific conferences. All results will be reported in accordance with appropriate reporting guidelines to enhance the quality and transparency of our research.

## Ethical and legal considerations

The research team will be responsible for ensuring that research participants have the opportunity to address any sense of burden and maintain their well-being. Any changes to the study protocol, expected or unexpected serious events, or early termination of the study will be promptly reported to the ethics committees by the principal investigators.

Participating patients are covered by insurance, as there is a risk of an unintentional fall due to independent exercise at home. However, the selected exercises will be according to the physiotherapeutic assessment and the patients’ resources, which help to minimise the risk of falling. Before the patients carry out the selected exercises independently at home, they will practice them face-to-face under therapeutic supervision during an appointment. Patients also will receive information on safety measures.

All participants will be informed that study-related data will be stored in pseudonymised form and will only be used for scientific data analysis. The study data will be kept in a locked archive for 10 years at the study centre after completion of the trial and will then be deleted. Additionally, the EU General Data Protection Regulation will apply, and all participants will be explicitly informed about their rights.

## Discussion

This study protocol describes the development and piloting of a complex intervention that aims to promote physical activity, quality of life and participation in older people with impending or existing functional limitations in rural areas. With the emphasis on maintaining physical activity as crucial for preserving independence and self-care, this intervention will address health outcomes that are highly relevant to the older individuals.

As an intervention, a prescribable “hybrid model” is being tested for feasibility and acceptance in the real healthcare setting. A hybrid model refers to a combination of online physiotherapy sessions (video therapy) and independent home-based exercises by the patients following an individual digital exercise plan, based on a physiotherapeutic assessment. The hybrid model can be an alternative to on-site physiotherapy, especially in rural areas with very old people and long distances to physiotherapy.

This study is primarily intended to determine whether the intervention and study procedures are feasible and acceptable in routine care and how the intervention may need to be refined before a future definitive trial. Although a consecutive control group is included, the study is not powered to test effectiveness between groups. Rather, the control group serves to contextualise feasibility findings and outcome trajectories under usual care.

The intervention addresses three fields of action: (1) primary prevention: general physical activation for the targeted prevention of loss of function, falls and osteoporosis, as well as social activation to prevent loneliness in old age and depression; (2) secondary prevention: targeted promotion of coordination, balance, mobility, strength and endurance in the case of existing limitations or reduced function; and (3) continuation of training in the home environment following inpatient or outpatient rehabilitation in order to achieve better sustainability of the effects.

Developing complex interventions is a challenging task. Therefore, our study underwent a careful intervention development process that included the proposed core elements in the updated MRC Framework for the development and evaluation of complex interventions [32]. These elements are identifying the context, engaging relevant stakeholders in the development process, creating a logic model, and considering the cost perspective. A particular strength of the present study is the explicit co-production process with older people and healthcare professionals, combined with usability pretesting and mixed-methods feasibility evaluation.

By using this methodological approach that includes pre-testing and piloting in a real healthcare environment, as well as evaluating patient-relevant outcome measures and combining quantitative and qualitative analyses, we expect to obtain reliable results regarding the feasibility, acceptability and potential benefits of the developed intervention in terms of social and physical activation. The findings will be used to refine intervention components, optimise implementation procedures, and inform the design of a future randomised controlled trial.

Thanks to the close cooperation between science, technology, and service providers, the project has the potential to make an important contribution to the further development of healthcare for older people in the region in order to secure and recruit skilled workers. In future, the intervention could be prescribed by the physician and, due to its independence of time and place, close a gap in the healthcare system.

